## Abstract

**Introduction:**

Comprehensive approaches for patients with psychotic symptoms play essential roles in the symptomatic and functional outcomes of patients, especially during disease onset. In Japan, the shortage of mental health services, particularly for outpatients, and community-based supports has been a major problem. The purpose of this trial is to investigate the effectiveness and affordability of 18-month comprehensive early intervention services for patients with first-episode psychosis compared with typical treatment.

**Methods:**

This interventional, parallel, single-blinded (open but blinded raters trial) was effectively designed. The participants are patients with a diagnosis of F2 or F3 (International Classification of Disease, 10 th revision), with psychotic symptoms. The inclusion criteria were an age of 15-35 years, onset of psychotic symptoms within 5 years, first-episode psychosis, and residence in the catchment area of each site. Allocation will be conducted equally between case management and standard care groups. After enrollment, standard care will be provided for both groups, and community-based care to promote recovery for 18 months will be provided for the comprehensive approach group. The primary outcome will be the function domain of the global assessment of functioning scores at 18 months after enrollment. Data assessment will be performed at enrollment and 18, 36, and 60 months after enrollment. The target sample size will be 150, and registration will occur from March 1, 2011, to September 30, 2012.

**Discussion:**

This trial will provide promising results about the effectiveness and cost-effectiveness of early intervention services in Japan to improve the quality and quantity of community mental health services.

**Trial registration:**

This trial was registered in The University Hospital Medical Information Network Clinical Trials Registry (No. UMIN000005092).

## Introduction

Comprehensive approaches for patients with schizophrenia play essential roles in their symptomatic and functional outcomes[1-4]. Particularly after the onset of psychosis, most patients and their families are extremely confused and distressed because of the conditions of patients and the lack of knowledge about their illnesses. Several randomized controlled trials (RCTs) have suggested that intensive community-based care for patients with first-episode psychosis (FEP) improve patient symptoms[5,6] and functional outcomes such as relapse, readmission, dropout from services, and social and vocational functioning[5-8]. Furthermore, additional analyses of cost-effectiveness revealed that patients with FEP who received intensive care had better outcomes without increase costs[9]. On the basis of these results, the use of early intervention services (EIS) has increased, especially in England[1].

Japan has among the best medical services in the world (e.g., the longest average life expectancy and smallest perinatal mortality rate). However, the shortage of mental health services for outpatients has been a major problem. In Japan, there are approximately 350,000 psychiatric beds, and approximately 210,000 patients majorly diagnosed with schizophrenia remain in psychiatric hospitals for more than 1 year (Reported from the Minster of Health, Labour, and Welfare). One issue preventing the discharge of patients with severe mental illnesses from hospitals is the shortage of community mental health services with psychosocial approaches, including family support despite the vast medical resources of Japan[10]. To change this situation and broaden EIS based on community settings, an RCT is needed to confirm the clinical effectiveness and affordability of EIS compared with existing hospital-based mental health service systems in Japan. Additionally, these trials must examine whether these specialized community mental health services will sustain the functional recovery of patients even after they finish 18-month support.

## Methods

### Trial design

This trial is designed with effectiveness, interventional, parallel, single-blinded (open but blinded raters) trial. The allocation of participants will be equal (1:1) between the comprehensive approach (CAP) and standard care (SC) groups. The entire trial design is illustrated in Figure 1. After enrollment, all participants will be provided standard care, and in the CAP group, comprehensive community-based care by an early intervention team will be provided for 18 months. Eighteen months after enrollment, all participants will be provided standard care only. The assessment of clinical data will be conducted at enrollment and 18 (first end point), 36 (second end point), and 60 months after enrollment (last end point). The target sample size will be 150, and registration will occur from March 1, 2011, to September 30, 2012. The last follow-up date will be September 30, 2017. This trial was registered in the University Hospital Medical Information Network Clinical Trials Registry (UMIN-CTR) accepted from the International Committee of Medical Journal Editors (ICMJE) (No. UMIN000005092).

**Figure 1 F1:**
[figure not shown]
**Entire design of this trial**.

### Participants

The participants are patients who received a diagnosis of F2 or F3 (International Classification of Disease, 10 th revision)[11], with psychotic symptoms, at 4 sites: the University of Tokyo Hospital, Tokyo Metropolitan Matsuzawa Hospital, Mie Prefectural Mental Medical Center, and Hinaga General Center for Mental Care and Sasagawa Clinic. The relevant details of the sites are summarized in Table 1.

**Table 1 T1:** Characteristics of facilities, number of patients, and number of staff members on early intervention teams at each site

		Univ of Tokyo	Matsuzawa	Mie	Hinaga
Beds in closed wards		29	713	200	255

Beds in open wards		31	149	200	300

Annual	Total	1107	2150	896	706
	
hospital	15-35 years old	381	445	165	184
	
admissions	F2	129	212	55	94

Average number of daily patients the in outpatient unit		170	329.4	214.2	309.8

Average number of daily participants in the outpatient rehabilitation center		33.1	57.6	49.9	109.6

Annual new patients	Total	1102	5656	1405	1150
	
	15-35 years old	474	NA	476	450
	
	F2	124	NA	43	58

Catchment area		Bunkyo, Arakawa, Taito, and Chiyoda	Setagaya, Suginami, Ota, Meguro, Shibuya, Komae, Chofu, and Mitaka	Tsu, Matsuzaka, Suzuka, Iga, Nabari, and Ise	Yokkaichi, Suzuka, Kameyama, and Mie-gun

Population (× 1000)		800	3020	870	620

	Psychiatrists	6	5	1	3
	
	Nurses	0	4	5	6
	
	Psychologists	3	0	1	2
	
Members of the EIS team	Psychiatric social workers	1	2	3	2
	
	Vocational workers	0	0	1	1
	
	Pharmacist	0	0	1	0

Abbreviations: Univ of Tokyo, the University of Tokyo Hospital; Matsuzawa, Tokyo Metropolitan Matsuzawa Hospital; Mie, Mie Prefectural Mental Medical Center; Hinaga, Hinaga General Center for Mental Care and Sasagawa Clinic; EIS, early intervention service.

Eligibility criteria are summarized in Table 2. The inclusion criteria are an age of 15-35 years old, onset of psychotic symptoms within 5 years, first-episode psychosis, and residence in the catchment area of each site (Table 1). Psychotic symptoms are defined by the first clear evidence of a positive psychotic symptom (i.e., delusion, hallucination, or thought disorder) that was scored 4 or higher on the positive and negative symptom scales (PANSS) [12] regardless of its duration.

**Table 2 T2:** Summary of eligibility criteria.

Inclusion criteria:

1. Residence in the catchment area of each site (also see Table 1)

2. Age between 15 and 35 years old

3. Within 5 years of the onset of psychotic symptoms

4. FEP

Exclusion criteria:

1. Premorbid IQ below 80

2. Unable to sufficiently communicate in Japanese

3. Require care for any organic mental disorder

4. Require inpatient care for any physical condition

5. A history of dependency on alcohol and/or other substance of abuse

6. Under physical restraint and/or seclusion

7. Received electroconvulsive therapy and/or transcranial magnetic stimulation therapy within the past month

8. Present involuntary hospitalization

9. Not having received an explanation of his or her condition or diagnosis by a psychiatrist

10. Regarded as inappropriate by medical doctors in charge for any other reason

Target patients: Patients with a diagnosis of F2 and F3 (International Classification of Disease, 10 th revision), with psychotic symptoms.

Exclusion criteria are premorbid IQ [13,14] of less than 80, inability to sufficiently communicate in Japanese, requirement of care for any organic mental disorder or inpatient care for any physical condition, a history of dependency on alcohol and/or other substance of abuse, under physical restraint and/or seclusion, received electroconvulsive therapy and/or transcranial magnetic stimulation therapy within the past month, present involuntary hospitalization, not having been given the explanation of his or her condition or diagnosis from a psychiatrist, and being regarded as inappropriate by their doctors for any other reason. Although the use of illegal substances such as cannabis among young people has been a major problem, a very small number of young people have used these drugs in Japan. Therefore, we adopted a history of continuous substance abuse as one of the exclusion criteria in this trial.

All of the eligibility criteria will be assessed by psychiatrists at each site; to complement these criteria, the laboratory data of all patients will be assessed within 30 days of enrollment, and a brain CT or MRI will be performed within 12 months.

### Ethical consideration

All participants will be presented with written informed consent to the ethical committee of each site (Univesity of Tokyo, No. 3307; Matsuzawa, No. 22-23; Mie, H23.2.21; Hinaga, H22.12.22) according to the Declaration of Helsinki after receiving a complete explanation of this trial.

### Intervention

For the CAP group, we will provide specialized early intervention teams by well-trained case managers and psychiatrists about their symptoms and daily activities for 18 months after enrollment. Case managers will promote participant recovery and social participation in cooperation with the early intervention team by using combination of cognitive behavioral therapeutic (CBT) approaches, psychoeducational approaches, family interventions, discharge support, and pharmacological therapy in accordance with the guidelines for FEP. The details of comprehensive community-based care are described later in the text. After 18 months, the participants will receive only standard care at each site. For the SC group, we will provide only standard care at each site throughout the entire study.

#### CBT approach

Several researches have suggested that CBT adapted to patients with early psychosis has effectiveness regarding their persistent positive symptoms, anxiety, and/or depression[15]. In this trial, we will not adopt structured CBT but needs-based CBT approaches in comprehensive community-based care. Case managers will receive basic CBT training and use the skills and techniques of CBT in comprehensive community-based care. The range and intensity of CBT will vary according to participant need as assessed by the early intervention team. Through CBT sessions, case managers will provide monitoring and coping skills for patients regarding their symptoms as well as functional skills for their daily lives.

#### Psychoeducational approach

Young people and their families rarely learn about symptoms, outcomes, and methods of coping with psychosis until they have mental illnesses; in other cases, they received incorrect information in addition to being subjected to discrimination and stigma. Therefore, they have significant stress and confusion because of the lack of information about psychosis. Several studies have suggested that psychoeducation is effective for relapse prevention, reducing hospital admission, and adherence of medication[16-18]. In this trial, the psychoeducational program for people with FEP will consist of sessions that provide not only information about etiology, symptoms, treatments, and outcome of psychosis, but also positive and helpful information toward functional recovery. In addition, we will provide psychoeducational programs for their families as described in the following section.

#### Family intervention

Family interventions will consist of 2 main domains of psychoeducation and family support for the family members of patients with mental illnesses. As described above, family members usually have little correct knowledge but a plethora of incorrect information and a great deal of stigma. Therefore, family members are also confused about methods of assisting patients who have recently exhibited psychotic symptoms. Several studies have suggested that family intervention for early psychosis is effective for relapse prevention, reducing hospital admission, and adherence of medication[19-21]. Family interventions for early psychosis will consist of psychoeducational programs and psychological therapy or counseling for families to relieve their burdens regarding the care of people with psychosis. Psychoeducational programs for families will consist of lectures about psychosis and peer group sessions. Psychological therapy and counseling for families will be provided through individual sessions.

#### Discharge support

More than 210,000 patients with schizophrenia stay in hospital for more than 1 year in Japan, mainly because of a lack of community mental health services[10]. This is particularly true for patients with psychosis for whom their family members are unable to obtain information and support from psychiatric community services. In this trial, case managers will encourage patients to live in their communities by introducing additional psychiatric community services, if needed.

#### Pharmacological therapy in accordance with the guidelines for FEP

Several pharmacological guidelines for schizophrenia and mood disorder are available worldwide. However, some psychiatrists in Japan have developed experimence-oriented strategies that result in polypharmacy for patients with schizophrenia[22]. Polypharmacy can exacerbate the negative symptoms and cognitive impairments of patients in addition to promoting dropped-out from treatment[22]. One reason why psychiatrists tend to prescribe more tablets may be that patients' treatment strategy and prescription are mainly decided by their psychiatrists who know little information except from the consultation with patients and their family members. In this trial, we will conduct regular meetings with early intervention teams and propose treatment and prescription strategies to psychiatrists according to the guidelines to eliminate unnecessary prescriptions.

#### Strategy for replacement from EIS

Recent studies about EIS for patients with FEP had negative results regarding the effectiveness of EIS discontinued in a longer term[23,24]. One reason may be that it is difficult to prepare patients to finish EIS and switch to normal services. On the basis of this result, we will emphasize "graduating from the EIS" and provide the policy of EI services to switch over to usual community services in order to easily maintain the effectives of EIS. Thus, we will also investigate whether this strategy for switch over will prolong the effectiveness of EIS.

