## Discussion

This trial has some possible limitations regarding sample size and the duration of case management. Previous studies of EIS for patients with FEP have suggested that although 1.5-year EIS improved patient social functions and readmission rates, these effects did not persist (5 years)[23,24]. However, these results also depend on the treatment provided to the control group, and community mental health services are widely available in Holland and England[1]. In the present situation in Japan, little psychological education is provided in schools and the workplace, and few mental health services are available in the community setting; consequently, much prejudice, discrimination, and stigma exists regarding psychosis[10]. In addition, we will emphasize "graduating from the service" in that case managers will continue to provide services after EIS after a participant enrolls in the trial. Therefore, this trial will demonstrate the effectiveness of EIS in Japan and also explore and consider exit strategies for EIS. Finally, the results of this trial will be used to inform policy makers and practitioners about the benefits, required human resources, and cost-effectiveness of EIS. This trial will provide helpful results about the effectiveness and cost-effectiveness of EIS in Japan to improve the quality and quantity of community mental services.

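### The two-arm design can show whether the effect of EIS with its planned switch-over lasts, but not whether the switch-over strategy itself prolongs it, as one sentence in the Methods says it will

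*Protocol article*

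**What the plan says.** The section Strategy for replacement from EIS notes that earlier trials lost their effect once EIS ended, and offers poor preparation for leaving the service as one reason. The team will therefore stress graduation from EIS and "provide the policy of EI services to switch over to usual community services in order to easily maintain the effectives of EIS". The section ends by saying that "we will also investigate whether this strategy for switch over will prolong the effectiveness of EIS".

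The arms are set out under Trial design and Intervention:

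- Allocation: "The allocation of participants will be equal (1:1) between the comprehensive approach (CAP) and standard care (SC) groups".
- CAP: "in the CAP group, comprehensive community-based care by an early intervention team will be provided for 18 months".
- SC: "For the SC group, we will provide only standard care at each site throughout the entire study".
- After the intervention period: "Eighteen months after enrollment, all participants will be provided standard care only".

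Under Outcomes and measurement items, GAF-F at 36 and 60 months is a secondary outcome. The Introduction gives the long-term question at the level of the service: whether recovery holds once the 18 months of support have ended. The Discussion says that "this trial will demonstrate the effectiveness of EIS in Japan and also explore and consider exit strategies for EIS".

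**The concern.** The grammatical subject of the sentence in the Methods is the switch-over strategy, not the CAP package. It promises an answer about the added effect of one component on how long benefit lasts. To learn that, one must compare people who leave EIS with the strategy and people who leave EIS without it. The design as described has no second group of that kind.

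What is at stake is how the results at 36 and 60 months are read. If a CAP-SC difference persists, the sentence makes it natural to credit the strategy, although the rest of the package or weak standard care in the comparison arm could produce the same result. If the difference fades, it would be equally natural to conclude that the strategy failed, although the fading might have been faster without it. Neither conclusion would follow from the data.

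**Working it through.** The protocol gives no figure for this aim, so there is none to reproduce. The planned sample size of 150 is not an input, because the question is what can be identified and not how precisely. The check is to list what each arm receives and see which contrasts exist.

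**Inputs**

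- Two arms, 1:1 (Trial design).
- CAP: EIS for 18 months, with the switch-over described as service policy and no exempt subgroup (Trial design; Strategy for replacement from EIS).
- SC: standard care only throughout (Intervention).
- Standard care only for everyone after month 18 (Trial design).
- Stratification by site and by inpatient or outpatient status; no second randomisation (Randomization).
- Tests at each end point, with regression for possible confounders; no analysis of the strategy (Statistical method).

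**Cells.** Let E = 1 if EIS is given and S = 1 if the switch-over strategy is given.

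| Cell | E | S | In the trial? |
|---|---|---|---|
| CAP | 1 | 1 | Yes |
| SC | 0 | 0 | Yes |
| EIS without the strategy | 1 | 0 | No |

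**Contrast.** Let m(E,S) be mean GAF-F at a given later end point. Then

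CAP − SC = m(1,1) − m(0,0) = [m(1,0) − m(0,0)] + [m(1,1) − m(1,0)].

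The first bracket is the effect of EIS alone. The second is what the strategy adds, and it is the quantity named in the stated aim. Both brackets contain m(1,0), for which the trial has no participants. Only their sum is estimated.

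Suppose the sum at 36 months is D. The splits (D, 0), (0, D) and (D/2, D/2) all imply the same means in CAP and SC, so the data cannot tell them apart. More participants narrow the interval for D and leave the split unknown.

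**Change over time.** The word prolong might suggest comparing D at 18 months with D at 36 or 60 months. That shows whether the package effect is maintained. Each of those differences is again a sum of the same two brackets, so the change over time does not isolate the second.

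**Other possible comparisons**

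- *Variation within CAP.* If delivery of the strategy varied in practice, a comparison inside CAP would not be randomised, and the article lists no measure of how far the strategy was delivered.
- *Earlier EIS trials.* No such comparison is planned under Statistical method. The Discussion itself cautions that "these results also depend on the treatment provided to the control group", and it contrasts the wide availability of community services in Holland and England with the few available in Japan.

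A fuller analysis plan could not repair this, since no analysis supplies a missing group. It is therefore not a detail that an article may leave to another document.

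**The case against.** The strongest case on the other side is that this is one sentence closing the description of an intervention component. The stated purpose is the effectiveness and affordability of the service as a whole, and the Introduction already puts the long-term question at that level. No outcome, sample size input or analysis is tied to the strategy alone. Read with the Introduction, the sentence may mean only that EIS with planned graduation will be followed to see whether its effect lasts. Moreover, a package trial cannot separate CBT, family intervention or discharge support either, and nobody counts that as a fault.

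Much of this stands, and it sets the size of the point. It does not remove it. The article announces no investigation of the separate effect of CBT or family work, but it does announce one for the switch-over strategy. The charitable reading is not what the sentence says, and the correction simply makes that reading explicit.

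A reader might infer more than the document supports in three ways:

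- *That the Discussion makes a causal claim about the exit strategy.* It promises only to explore and consider exit strategies, and what it says will go to policy makers is the benefits, staffing needs and cost-effectiveness of EIS. The exit strategy is not in that list.
- *That the plan will judge the strategy against the earlier trials.* No such analysis is described.
- *That the results at 36 and 60 months are uninformative.* They answer the package-level question.

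**Conclusion.** The point holds as a minor correction to a secondary aim. The Methods state that the trial will investigate the strategy's own effect on duration, and the design cannot identify that effect at any sample size. What it can estimate is the CAP-SC difference at 36 and 60 months for EIS and switch-over together.

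The conclusion rests on one reading. No single sentence says that every CAP participant receives the strategy; this is taken from its description as service policy with no exception. If delivery did vary, the conclusion would still hold, because the variation would not be randomised.

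The primary comparison at 18 months, the randomisation, the data collection and the planned analyses are unaffected.

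**What to change.** Replace the last sentence of Strategy for replacement from EIS with wording such as:

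> The trial will estimate whether the difference in GAF-F between the CAP and SC groups persists at 36 and 60 months, after 18 months of EIS delivered with a planned switch-over to usual services. It cannot separate the effect of the switch-over from that of EIS.

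This agrees with the long-term question in the Introduction and with the secondary outcomes already listed. The Discussion needs no change, provided that its remark on exit strategies is read as exploratory.

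The cost is one sentence of text. No participants, assessments or analyses are added, and the sponsor gives up only a claim that the design could not support.
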